### 2.4. Primary and secondary endpoints

The primary endpoint is local recurrence of grade 2 or 3 AIN 6 months after the procedure. The secondary end points are presented in Table 2.

**Table 2 T2:** Secondary outcomes.

Objective	Endpoint	Rationale for the endpoint
To assess the efficacy of ablation therapy	Metachronous recurrence† of grade 2 or 3 anal intraepithelial neoplasia at 6 mo after the procedure	It is not a subjective endpoint
To assess safety after ablation therapy	Occurrences of adverse events	It is necessary to evaluate safety
To assess the efficacy of ablation therapy	Local recurrence of grade 2 or 3 anal intraepithelial neoplasia at 3 mo after the procedure	It is not a subjective endpoint
To assess the efficacy of ablation therapy	Metachronous recurrence of grade 2 or 3 anal intraepithelial neoplasia at 3 mo after the procedure	It is not a subjective endpoint

† A metachronous recurrence is defined as a recurrence outside of the ablative area.

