## Abstract

**Methods::**

This single-arm, open-label, pilot intervention study will investigate the efficacy and safety of electrocautery ablative therapy using high-frequency medical devices. Patients diagnosed with grade 2 or 3 AIN will be included and will receive ablation treatment. Then, they will be followed up at 3 and 6 months after the procedure for HRA-guided sextant biopsy. To reduce the possibility of missed lesions before and after the intervention, we will perform HRA-guided sextant biopsy routinely. In this study, a sextant biopsy is defined as at least 6 biopsies in all directions, regardless of abnormal findings under HRA. The primary outcome is the recurrence rate at 6 months, and the secondary outcomes are the adverse event and recurrence rates at 3 months.

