#### 2.2.2. Inclusion criteria

Patients who meet the following criteria will be eligible to participate in the study.

Persons or their legal representatives who provide written consent for the participation of the patient in the trial.Persons aged 20 years of age or older at the time consent was obtained.Persons diagnosed with grade 2 or 3 AIN based on sextant biopsy results under HRA within 1 year. Sextant biopsy is defined as at least 6 samples in all directions, regardless of abnormal findings.

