#### 2.2.4. Study protocol

Table 1 shows the study schedule. A physician will explain the study protocol to each candidate, and if consent is obtained, the physician will ask the candidate to sign an informed consent form and perform the examination in keeping with the description in Table 1. At visit 1, patients with AIN will undergo electrocautery ablation. At visits 2 and 3, a physician will confirm adverse events due to the intervention and perform HRA with a biopsy.

**Table 1 T1:** Study schedule.

	Screening	Visit 1 (day 1)	Visit 2 (day 90)	Visit 3 (day 180)
			±45 days	± 45 days
Informed consent	x			
Confirmation of eligibility (inclusion and exclusion criteria)	x			
Enrollment	x			
Clinical characteristics	x			
Vital signs		x	x	x
Physical findings	x	x	x	x
Electrocautery ablation		x		
Adverse events		x	x	x
High-resolution anoscopy			x	x
Tissue biopsy			x	x

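### Metachronous recurrence is defined by location alone, so HSIL outside the ablated area that was already present at entry can be counted as recurrence and read as ablation efficacy

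*Protocol article*

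**What the plan says.** Section 2.4 makes local recurrence of grade 2 or 3 AIN at 6 months the primary endpoint. Table 2 adds two rows for disease elsewhere in the canal: "Metachronous recurrence of grade 2 or 3 anal intraepithelial neoplasia at 3 mo after the procedure", and the matching row "of grade 2 or 3 anal intraepithelial neoplasia at 6 mo after the procedure". Both carry the objective "To assess the efficacy of ablation therapy". The footnote supplies the only definition: "A metachronous recurrence is defined as a recurrence outside of the ablative area". The article does not define recurrence itself.

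On entry status, section 2.2.2 admits "Persons diagnosed with grade 2 or 3 AIN based on sextant biopsy results under HRA within 1 year" and adds: "Sextant biopsy is defined as at least 6 samples in all directions, regardless of abnormal findings". Table 1 marks HRA and tissue biopsy only at the two follow-up visits, and section 2.2.4 agrees: "At visits 2 and 3, a physician will confirm adverse events due to the intervention and perform HRA with a biopsy". The Abstract gives the purpose of the sextant approach: "To reduce the possibility of missed lesions before and after the intervention, we will perform HRA-guided sextant biopsy routinely".

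On treatment, section 2.3.1 describes a magnified acetic-acid examination before the ablation area is chosen, and ablation of that area with a 3 to 5 mm margin. Extensive lesions may be treated in stages, the second stage usually coming within 3 months. Table 1 puts Visit 2 at day 90, plus or minus 45 days.

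**The concern.** A lesion is metachronous if it arises later, at a site that was previously clear. The footnote tests where the lesion is, not whether it is later. HSIL that was outside the ablated area from the start meets the location test just as well as new HSIL does.

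The two rows are two of the three efficacy endpoints in Table 2, and the Discussion (section 3) reports that in earlier studies most recurrences lay outside the treated area. This category may therefore hold many of the trial's events. If part of it is disease that was never treated, a reader could take the 3- or 6-month rate as early failure of the device or rapid new disease, when neither happened. The Discussion also presents sextant sampling as what lets this trial show an accurate clinical course, and mixing pre-existing with new disease weakens that claim.

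**Working it through.** The plan gives no figure on this point to reproduce. The check is a reading of the rules, followed by an illustration on stated assumptions.

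**Route 1: known disease not yet ablated.** Visit 2 may fall from day 90 − 45 = 45 to day 90 + 45 = 135. The second stage is usually done within 3 months, roughly by day 90, and the text allows it to be later. The two periods overlap from day 45 onwards. A patient can be biopsied at Visit 2 while a known lesion awaits its second stage. That lesion lies outside the area ablated so far, so the footnote lets it count at 3 months. This route needs no assumption about biopsy sensitivity.

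**Route 2: disease missed at entry, or arising between the entry biopsy and ablation.** The qualifying biopsy may be up to a year old, and the schedule does not repeat it before ablation. Six samples do not exclude disease. If they fell at random and independently (an assumption; targeting by HRA would lower these figures), all six would miss a lesion covering a fraction *f* of the area with probability (1 − *f*)^6:

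| *f* | P(all six miss) |
|---|---|
| 5% | 0.74 |
| 10% | 0.53 |
| 20% | 0.26 |
| 30% | 0.12 |

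**Size of route 2, by assumption.** Let *p* be the share of patients with a second HSIL focus at entry, and *s* the chance that a sextant set detects it. Neither is in the document. The share carrying an undetected focus forward is *p*(1 − *s*). If follow-up biopsy has the same sensitivity, the share scored at one visit is *p*(1 − *s*)*s*.

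| *p* | *s* | Carried forward | of 20 | Scored at one visit | of 20 |
|---|---|---|---|---|---|
| 10% | 80% | 0.020 | 0.4 | 0.016 | 0.3 |
| 10% | 50% | 0.050 | 1.0 | 0.025 | 0.5 |
| 30% | 80% | 0.30 × 0.20 = 0.060 | 1.2 | 0.060 × 0.80 = 0.048 | 1.0 |
| 30% | 50% | 0.30 × 0.50 = 0.150 | 3.0 | 0.150 × 0.50 = 0.075 | 1.5 |

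These figures make no allowance for foci found and treated at the acetic-acid examination, which would lower them.

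**Effect on the reported rate.** With a share *r* scored because of pre-existing disease and an independent rate *m* of truly new disease, the observed rate is 1 − (1 − *r*)(1 − *m*). Take *r* = 0.05, which lies inside the range above:

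- *m* = 0.05: observed 0.098; patients with pre-existing disease are 0.05/0.0975 = 51% of those counted.
- *m* = 0.10: observed 0.145; 34%.
- *m* = 0.20: observed 0.240; 21%.

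In 20 patients each miscounted patient moves the rate by 1/20 = 5 points.

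**The case against.** The strongest reply is that the plan already guards against this. Before the area is set, section 2.3.1 has the canal examined again under magnification with acetic acid, so a focus visible that day can be included even if the old biopsy missed it. This stands: it would be wrong to infer that a focus missed at entry is never treated. What escapes is disease not seen at that examination, and disease seen but left for a later stage.

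Second, the footnote speaks of a recurrence, which in ordinary use implies earlier clearance, and a full protocol not shown here may say more. It would be too strong to say that all HSIL outside the area must be reported as new. But the article does state a definition, and that definition contains no clearance condition, so such disease *can* be counted.

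Third, local and metachronous events are kept apart, the primary endpoint is local only, and the trial is a 20-patient pilot reporting estimates and confidence intervals with no test or threshold. This also stands. It limits the consequence to the two secondary rows; it does not make their label or objective right.

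Fourth, a negative entry sample cannot prove that a site was clear, since six samples can miss disease. This is correct, and any reclassification must not claim otherwise.

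**Conclusion.** The point holds for the two metachronous rows of Table 2. As written, HSIL outside the ablated area that was present at entry can be counted as recurrence after ablation and listed under its efficacy. The baseline sextant biopsy and the examination at ablation reduce this without removing it. The primary endpoint as defined in section 2.4 is not affected.

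The size cannot be derived from the document. The illustrative 1.0 to 1.5 of 20 patients per visit rests on an assumed 30% with a second focus, 50% to 80% sensitivity at both entry and follow-up, and no help from the acetic-acid examination. A reader might take the larger 1.2 to 3.0 of 20 as the number miscounted. That is the number carrying an undetected focus, and it equals the number scored only if follow-up detection is perfect. A reader might also infer that the 3-month rate must be hit hardest. The staging overlap does expose that visit specifically, but nothing in the document lets the two visits be compared in size.

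**What to change.** Relabel the two rows *grade 2 or 3 AIN outside the ablated area*, with the objective *occurrence of HSIL outside the treated area*. Replace the footnote with a split by entry biopsy status at the same position:

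- **(a) Entry-positive and not fully ablated:** persistent or untreated. This includes the unablated part of a partly ablated sextant and lesions awaiting a second stage.
- **(b) Entry-negative:** new or previously undetected. Use this label at both visits, without claiming that a negative entry sample shows the site was clear.
- **(c) Entry position not recorded:** undetermined.

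Separately, the staged-ablation timing in section 2.3.1 and the Visit 2 window in Table 1 must be reconciled with the 3-month endpoint. How to do so is for the investigators.

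The cost is the wording of one footnote and two rows, with no new procedure. The local/metachronous split already requires follow-up position to be known. Entry position is less certain: samples are taken in all directions, but neither section 2.2.2 nor the data list in section 2.5 says that results are recorded by position, so this should be confirmed; class (c) covers the cases where they were not. The remaining drawbacks are small categories in 20 patients, and that class (a) may contain some truly new disease in a sextant that was positive at entry.

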### 2.5. Data collection and management

A case report form (CRF) will be prepared by appropriate and authorized individuals (investigators and physicians). Unless data recorded directly in the CRF are used as the source material, all data recorded in the CRF must be consistent with the original material. During the course of the study, the investigator will collect data at each visit. All study findings and documents will be kept strictly confidential, and patients will be identified only by their patient number and/or birth date, never by name. To protect participant anonymity, the investigator will keep patient-identifying documents confidential.

The following data will be collected.

Date of birth (age), sex, nationality, race, prior medical history, history of current disease, complications, allergy, and pregnancy status;Body weight and height at the first visit;Vital signs at every visit;Level of consciousness;Body temperature (°C);Blood pressure (mm Hg);Pulse rate (beats/min);Respiratory rate; andPhysical condition at every visit (Physical conditions will be examined by inspection, palpation, auscultation, and percussion.).

### 2.6. Statistical analysis plan

The population to be analyzed is defined as all patients receiving electrocautery ablation. The characteristics of the study participants will be summarized using descriptive statistics. The recurrence rate at each visit will be estimated using point estimates and 95% confidence intervals. The safety analyses will be based on this analysis set. Adverse events will be stratified according to the patients’ HIV status and severity. Analyses will be categorized and aggregated by patient ID, and a list of outcomes will be generated. Data will be analyzed with STATA, version 16.0, and the sample size calculation will be determined using PASS 2022.

## 3. Discussion

The detection of AIN by screening is key to the prevention of anal cancer. Based on the similarity of cervical cancers, screening programs with interventions such as electrocautery ablation may be a favorable approach in high-risk populations. The ANCHOR study showed that interventions in patients with HSIL significantly reduced the risk of anal cancer. Electrocautery ablation is a promising intervention, particularly when the targeted area is extensive. Several studies have suggested high efficacy and low side effects.^[5,8,10]^ The major concern is the high rate of relapse, and according to previous studies, most recurrences occurred outside of the treated area.^[8,10]^ In our protocol and routine practice for HRA-guided biopsy, biopsy will be conducted in all directions regardless of HRA findings; thus, the results of this study will reflect an accurate clinical course based on pathological findings. This is the big difference between our study and other previous studies.^[5,8,10]^ Furthermore, in this study, the Surgitron dual EMC will be used for electrocautery, and the device has a high radiofrequency, which is expected to reduce postoperative discomfort, scar tissue formation, and enhanced healing while maintaining high efficacy.^[12]^

Several potential limitations of this study need to be acknowledged. First, the study is not a randomized controlled trial or single-arm trial. Therefore, the effectiveness of electrocautery ablation using the Surgitron dual EMC compared with another device is unknown. However, this study will evaluate safety first. Second, since this is a single-arm study with a small sample size, the result will likely be affected by selection biases. Third, the study population will include MSM with and without HIV. Other important at-risk populations include women with HPV-related cancer or precancerous lesions, people with immunosuppression, and people taking immunosuppressants who will not be included in this study. Further studies are needed to overcome these limitations.

## 4. Conclusion

In this study, we will treat HSIL patients with electrocautery ablation using the Surgitron dual EMC and follow-up with HRA-guided biopsy to determine the efficacy and safety of electrocautery ablation.
